### Sample Size and Power Calculation

This trial aims to recruit 128 participants with mild AD and their carers, with 64 patients being allocated to each study group. A study of this size will have 80% power to detect between group differences on the ADAS-COG associated with moderate effect size (Cohen's d = 0.5) and alpha of 5%.

### Analysis of the Data

Changes in the ADAS-COG score from baseline are the primary outcome of interest in the study. We will model these changes at 2 time points: 13 (immediately after the intervention comes to an end) and 26 weeks. We will use mixed effects models to analyse the data. This approach will enable us to take into account the cognitive performance of participants at baseline, as well as the intra-person correlation generated from repeated measures. Intention-to-treat (ITT) analyses will be based on the use of imputation by chain equations (ICE), which will precede the use of the mixed-effects model. The ITT will be the primary analysis of the study.

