### Intervention

Following the baseline assessment, dyads (person with mild AD and companion) are randomised to one of two intervention groups. The intervention consists of a twelve-week CA program. Sessions are run by facilitators experienced in conducting research with older adults. The two groups are exposed to the same length of intervention, social interaction and contact with the program facilitators. The program was developed by a qualified Neuropsychologist (MV) and a manual produced. All of the sessions are delivered in a structured way for consistency, and audio-taped for subsequent fidelity assessment.

Research assistants (RAs) blinded to group allocation conduct all assessments. RAs are provided with strict instructions to avoid any potential opportunity for disclosure regarding intervention participation. Following completion of the trial, RAs undertaking data collection will be asked to identify the group membership of participants, to determine the effectiveness of the blinding procedures that were put in place for this project. A brief summary of each intervention group is provided below.

Participants with mild AD and their companions (Group 1): Each group consists of a maximum of five dyads taking part in 90-minute sessions once a week for seven weeks. Session One introduces the nature of the program and develops familiarity within the group, with personal introductions and sharing of background information and experiences. Sessions Two to Six focus on defining attention, processing speed, memory, language and executive functions. These sessions outline how these cognitive abilities are affected in AD and provide participants with strategies and techniques for managing declining capacity in each of these domains. Regular opportunity for supervised practice of such techniques and examples of activities to strengthen abilities occurs in all sessions. Dyads are also provided with an hour of home activities, to reinforce material learnt in the sessions. Sessions Seven to Eleven are completed by the participant with mild AD and their companion together in their own environment. Participants are provided with a workbook containing instructions and examples, along with phone calls from the facilitator once per week to address any questions and to monitor task completion. The final session (Session 12) offers an overview and discusses strategies to maximise participation.

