Companions of participants with mild AD alone (Group 2): This group consists of a maximum of five companions presented with the same session information and materials as Group 1. The only difference is that the companions attend the sessions with other companions, and are instructed to convey what is learnt during the sessions to the participant with mild AD during their home activities.

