### Randomisation

Randomisation is performed according to a random list of numbers generated by computer and undertaken in random blocks of 8 or 10 with no more than five dyads allocated to each group. The allocation list is handled by an independent investigator ([name]) who has no contact with study participants and is not involved in the supervision of staff responsible for the collection of data. The allocation table is then passed on to the facilitator running the intervention, who invites eligible participants to join the relevant groups. RAs undertaking the follow-up assessments remain blinded to group allocation.

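### Both arms are treated in groups of at most five, but the described primary model and the power statement make no allowance for correlation within a therapy group

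*Protocol article*

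**What the plan says.** The Intervention section of the protocol article sets out group delivery in both arms. For Group 1: "Each group consists of a maximum of five dyads taking part in 90-minute sessions once a week for seven weeks". For Group 2: "This group consists of a maximum of five companions presented with the same session information and materials as Group 1". The Group 2 sessions are attended by companions only, who pass the content on to the patient at home. Of the twelve programme sessions, seven are group sessions and five are done by the dyad at home with weekly telephone support.

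Under Randomisation, allocation is "undertaken in random blocks of 8 or 10 with no more than five dyads allocated to each group". The facilitator then invites participants to join the relevant group.

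Under Sample Size and Power Calculation, the article plans 128 patients, "with 64 patients being allocated to each study group". It states: "A study of this size will have 80% power to detect between group differences on the ADAS-COG", for a standardised effect of 0.5 at an alpha of 5%. No ICC or design effect appears.

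Under Analysis of the Data, change in ADAS-COG at 13 and 26 weeks is analysed by mixed effects models. The stated reason is that they can allow for baseline performance, "as well as the intra-person correlation generated from repeated measures". Therapy group and facilitator are not mentioned.

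**The concern.** Dyads are randomised individually but treated in small groups. Patients whose dyads or companions shared a therapy group may have outcomes that resemble each other more than those of patients from different groups. Group interaction is part of the programme: the first session builds familiarity among members, and techniques are practised under supervision.

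A model whose only dependence is within person treats patients from one therapy group as independent. If their outcomes are positively correlated for reasons specific to that group, the standard error of the arm difference is understated, the confidence interval is too narrow, and the 5% error rate of the primary comparison is exceeded. The power statement rests on the same independence, so the loss of information is not budgeted for either.

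**Working it through.** **Inputs from the article.** 64 patients per arm; standardised effect 0.5; alpha 5%; power 80%; groups of at most five in each arm; blocks of 8 or 10. An evenly split block gives m = 4 or 5 dyads per arm (inferred), so about 64/5 = 12.8 to 64/4 = 16 groups per arm, that is 13 to 16.

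**Assumption.** The article gives no ICC. The values 0.02, 0.05 and 0.10 are used as a range.

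**1. The plan's own figure.** For two independent means, power = Φ(0.5·√(64/2) − 1.96) = Φ(2.828 − 1.96) = 80.7%. The exact noncentral t with 126 degrees of freedom gives 80.1%. The stated 80% is therefore the two-sided test with independent patients; a one-sided test would give 88.2%.

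**2. Correlation specific to the therapy group, same ICC in both arms.** Design effect DE = 1 + (m − 1)·ICC. True error rate of a test that ignores groups = 2·[1 − Φ(1.96/√DE)]. Power when groups are allowed for = Φ(0.5·√(32/DE) − 1.96).

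| ICC | DE (m = 4 / 5) | True alpha | Power at 128 |
|---|---|---|---|
| 0 | 1 / 1 | 5.0% | 80.7% |
| 0.02 | 1.06 / 1.08 | 5.7% / 5.9% | 78.4% / 77.7% |
| 0.05 | 1.15 / 1.20 | 6.8% / 7.4% | 75.1% / 73.3% |
| 0.10 | 1.30 / 1.40 | 8.6% / 9.8% | 69.9% / 66.7% |

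A simulation (20,000 runs per setting, one value per person) gave error rates of 5.4% / 5.7%, 6.8% / 7.5% and 8.5% / 9.9% for the three positive ICCs, in line with the formula.

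The powers above use the normal approximation. A t reference with 2·(64/m − 1) degrees of freedom, which is roughly what small-sample corrections amount to when the group variance matters, gives 75.8% / 74.2%, 72.3% / 69.7% and 67.0% / 63.0%, about 3 to 4 points lower.

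**3. ICC in Group 1 only.** Group 2 patients do not attend sessions, so the other end of the range is no clustering there. With equal arms the variance of the difference is inflated by (DE + 1)/2:

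| ICC in Group 1 | Inflation (m = 4 / 5) | True alpha | Power at 128 |
|---|---|---|---|
| 0.02 | 1.03 / 1.04 | 5.4% / 5.5% | 79.6% / 79.2% |
| 0.05 | 1.075 / 1.10 | 5.9% / 6.2% | 77.9% / 76.9% |
| 0.10 | 1.15 / 1.20 | 6.8% / 7.4% | 75.1% / 73.3% |

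**4. Correlation shared by both arms of a block.** If the two groups from one block run over the same period, season and cohort effects are common to both and cancel in the arm contrast. Let B be the share of variance due to block and G the share specific to the therapy group. The variance of the contrast, relative to what the unadjusted test assumes, is (1 − B − G) + m·G. For m = 5 and B + G = 0.05:

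- all block: 0.95, true alpha 4.4%;
- half block, half group: 0.95 + 5·0.025 = 1.075, true alpha 5.9%;
- all group: 0.95 + 5·0.05 = 1.20, true alpha 7.4%.

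Only the group-specific part inflates the error rate.

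**The case against.** The strongest reply is that the Analysis section is a few lines in a journal article. It says what a mixed model makes possible and does not exclude a therapy-group term, which a fuller analysis plan may contain. That stands as a limit on the claim: the article does not say that within-person correlation is the only dependence to be modelled. It does, however, name the source of correlation the model is chosen to handle, and its sample size reproduces only under independence. Group delivery is a feature of the design, so the point is worth raising. What the imputation step contains is a different matter: silence on it in a condensed article is no finding.

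Second, there are reasons to expect a small ICC. Delivery is manualised, structured and audio-taped; five of the twelve sessions take place at home; the last assessment is at 26 weeks, well after the groups end; and clustering of Group 2 patients can only arise through their companions. If the same facilitator led groups in both arms, that person would add no arm-specific correlation. These arguments bear on size and are fair.

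A reader might infer more: that the groups are closed, that standard errors are certainly too small, that the 5% level is certainly not held, or that shared dates and season add to the problem. The documents do not support this. They do not say that groups are closed and give no ICC. If the paired groups run together, shared dates and season cancel in the contrast, and ignoring them makes the test slightly conservative.

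**Conclusion.** The point holds in conditional form. Treatment is group-delivered in both arms, the described primary model names no therapy-group term, and the power statement has no allowance for clustering. Any sufficiently large correlation specific to the therapy group makes the unadjusted test anti-conservative.

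The size depends on an ICC that has to be assumed. At 0.02 or below the true error rate stays under 6%, which is minor. At 0.05 it is about 6% to 7.4%, and at 0.10 about 7% to 10%, the lower end of each range applying if only Group 1 is clustered. These figures assume groups of 4 to 5 with stable membership (inferred from the blocks and the seven-session course) and no offsetting block effect.

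This is a change that should be made because it is cheap and protects the primary comparison. It is not a defect that invalidates the trial.

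**What to change.** Add a random effect for therapy group, nested in arm, to the primary mixed model. Use Kenward-Roger or Satterthwaite degrees of freedom, since there are only about 13 to 16 groups per arm. Include randomisation block, so that what both arms share is removed from the contrast. Report the estimated ICC. One common group variance is enough for the primary model. An arm-specific variance, motivated by the absence of Group 2 patients from sessions, can be a sensitivity analysis, because it would be weakly estimated from so few small groups.

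The change affects analysis wording only; group membership is known from the allocation. The cost is somewhat wider confidence intervals and an honest restatement of power at 128 patients: about 78% at an ICC of 0.02 in both arms, 73–75% at 0.05 and 67–70% at 0.10 by the normal approximation, and about 3 to 4 points less with small-sample degrees of freedom. The power section should give these figures with the ICC marked as an assumption.

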## Discussion

Cognition-focussed interventions are increasingly being adopted for the treatment of cognitive decline in older adults, with CST recently recommended as the treatment of choice for individuals with mild dementia [2]. However, the efficacy, sustainability of effect, and cost-effectiveness of involving and training a carer/companion to deliver cognitive tasks, and the degree to which cognitive changes can be maintained over time using this form of delivery, is yet to be established.

This trial has been designed according to CONSORT guidelines and has been structured to enable its reproduction in both research and clinical settings. We expect to complete recruitment by December 2011 and anticipate that the results of this study will have implications for health care policy and resourcing and facilitate improvements in the management of people with mild AD. The results of this study will enable us to determine, for the first time, if a CA intervention delivered to companions alone is as effective at promoting changes in cognitive function as an intervention involving both the person with dementia and his/her companion. These results will have important implications for the design of sustainable cost-effective health services for people with mild AD.

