**Methods/Design:**

The study will aim to recruit 128 community-dwelling men and women with probable AD according to NINCDS-ADRDS criteria. Participants will be randomly allocated to one of two cognitive activity treatment groups: (1) Participants with mild AD and their companions together (2) Companions of participants with mild AD alone. The intervention will consist of a twelve-week program of cognitive stimulation. Seven weeks of the program will involve 90-minute group sessions delivered once per week while the remaining weeks of the program will involve structured home based activities with telephone support. The primary outcome measure of the study is the change from baseline in the total score on the Alzheimer Disease Assessment Scale-Cognitive (ADAS-COG). Secondary outcomes of interest include changes in health related quality of life, mood, memory, language, executive functions, independent living abilities and psychiatric symptoms for participants with mild AD. Changes in companion quality of life, mood, and general health will also be monitored. Primary endpoints will be collected 13 and 26 weeks after the baseline assessment.

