**Discussion:**

The proposed project will provide evidence as to whether CST for people with AD and their companions is more beneficial than when used for companions alone. Outcomes sought include a reduction of further cognitive decline and improved quality of life amongst older adults with mild AD. We anticipate that the results of this study will have implications for the development of cost-effective evidence-based best practice to treat people with mild AD.

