Quayhagen and Quayhagen [8] had spousal caregivers apply cognitive stimulation techniques and found that improvements in memory, as well as additional aspects of cognition, could be achieved, with a home-based program. This study, however, was limited to spouses and a research team modelled the programme in the home of the dyad. For those patients who are widowed or single, access to a carer or companion may be limited to less contact hours. The feasibility of having instructors/team members provide one-to-one instruction may also restrict the availability of this type of facilitation.

We have designed a single-blind, randomized trial of an intervention drawing on principles of cognitive stimulation. The activities and intervention were selected with regard to suitability for older adults with mild Alzheimer's disease (AD) and designed in a manner that could be readily adapted for use in the home environment and implemented by a companion. The study aims to determine if a program of cognitive activity (CA) that includes both people with AD living in the community and a companion has better cognitive outcomes over six months for participants with dementia than a CA program delivered to companions only. Secondary outcomes for this trial include the quality of life and well being of people with AD and their companions.

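### The Discussion promises a verdict on equal effectiveness, but the aim and power calculation are for a difference and no non-inferiority margin is set

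*Protocol article*

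**What the plan says.** The Background section frames the question in one direction: whether the programme that includes both members of the dyad "has better cognitive outcomes over six months for participants with dementia than a CA program delivered to companions only". The Abstract's Discussion paragraph likewise asks whether joint delivery is the more beneficial of the two.

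Sample Size and Power Calculation follows that aim. It plans 128 dyads, 64 per group, giving "80% power to detect between group differences on the ADAS-COG" at Cohen's d = 0.5 and alpha 5%. Analysis of the Data plans mixed-effects models for change in ADAS-COG at 13 and 26 weeks, with intention to treat as the primary analysis. No section sets out a non-inferiority or equivalence hypothesis or a margin. Primary outcome measure calls a four-point ADAS-COG change over six months clinically relevant, but does not use it as a margin or link it to d = 0.5.

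The main Discussion then states that the results will make it possible to determine "if a CA intervention delivered to companions alone is as effective at promoting changes in cognitive function as an intervention involving both" members of the dyad, and links this to the design of cost-effective services.

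Both groups are active: "Participants will be randomly allocated to one of two cognitive activity treatment groups". The Abstract adds: "Outcomes sought include a reduction of further cognitive decline and improved quality of life amongst older adults with mild AD".

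**The concern.** Asking whether joint delivery is better and asking whether companion-only delivery is just as good are different statistical questions. The first is answered by rejecting the hypothesis of no difference. The second needs a stated margin and a confidence interval that excludes a deficit of that size. The article sets up the first and announces an answer to the second.

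The two come apart when the result is not significant. A reader following the Discussion could then take the null result as showing that companion-only delivery works equally well. The Discussion places this conclusion next to service design, so the inference could reach planning decisions without the evidence it needs.

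**Working it through.** **Inputs from the protocol article.** 64 per arm, d = 0.5, alpha 5%, 80% power (Sample Size and Power Calculation); four points as a clinically relevant change (Primary outcome measure). The article gives no SD for ADAS-COG change and no margin, so margins are shown in SD units and the conversion to points uses assumed SDs.

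**1. The plan's own figure.** For a two-sample t-test, two-sided 5%, d = 0.5:
- required n = 63.8 per arm, so 64 per arm and 128 in total;
- power at 64 per arm = 80.1%.

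A one-sided 5% test would need only 50 per arm (normal approximation). The stated size is therefore that of a two-sided test of difference, and it reproduces. It includes no allowance for dropout.

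**2. Precision at 64 per arm, full data.** The standard error of the difference in SD units is √(2/64) = 0.177. The 95% CI half-width is 1.96 × 0.177 = 0.35 SD.

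**3. Chance of a non-significant result when companion-only is truly worse** (1 − power, two-sided t-test, 64 per arm):

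| True deficit | P(non-significant) |
|---|---|
| 0.2 SD | 80% |
| 0.3 SD | 61% |
| 0.4 SD | 39% |

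**4. Power for a non-inferiority claim.** With true difference 0 and one-sided 2.5%, power = Φ(margin/0.177 − 1.96). The n for 80% power is 2 × (1.96 + 0.842)² / margin², rounded up.

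| Margin (assumed) | Power at 64 per arm | n per arm for 80% | Total |
|---|---|---|---|
| 0.20 SD | 20% | 393 | 786 |
| 0.25 SD | 29% | 252 | 504 |
| 0.30 SD | 40% | 175 | 350 |
| 0.40 SD | 62% | 99 | 198 |
| 0.50 SD | 81% | 63 | 126 |

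The planned size suits only a margin of about 0.5 SD. A margin that wide would accept as non-inferior a deficit approaching the effect the trial is designed to find.

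**5. If four points were used as the margin.** The article does not do this, and the SDs are assumptions:
- SD 6: margin 4/6 = 0.67 SD, power 96%;
- SD 8: margin 4/8 = 0.50 SD, power 81%;
- SD 10: margin 4/10 = 0.40 SD, power 62%.

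Whether the planned size is adequate for that margin therefore depends on an SD the article does not state.

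**The case against.** Several points on the other side are sound.

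- **It is one sentence of Discussion.** The aim, the Abstract's question, the power statement and the analysis all fit a test of difference, and none depends on that sentence. This stands, and it lowers the severity. The sentence still states what the trial will determine, and it disagrees with the aim.
- **The document does not say that a null result will be read as equality.** This stands. The sentence names no test and no decision rule. A reader might infer that the superiority test itself is meant to settle equal effectiveness, but the article does not say so. The risk is a misreading that the wording leaves open.
- **A reader might infer that the trial cannot address the question at all.** That goes too far. A significant result favouring joint delivery would answer it in the negative, and the confidence interval could be judged against a margin fixed in advance. At assumed SDs of 6 to 8, power to exclude four points is 81% to 96%.
- **The deficits of 0.2 to 0.3 SD may be clinically small.** At SDs of 6 to 8 they are 1.2 to 2.4 points, below the article's four. This stands: the figures show that non-significance is not equality, and do not show that a four-point deficit would be missed.
- **The calculation is simplified.** Baseline adjustment and repeated measures may narrow the interval; dropout would widen it. Neither makes non-significance evidence of equality.
- **Margins and interval rules may sit in an analysis plan that is not shown.** This holds for reporting rules. It is weaker for the margin, because the protocol article has already fixed the aim and the sample size as those of a test of difference.
- **A reader might also call the lack of an untreated arm a design error.** The documents do not support that. A head-to-head comparison of two delivery modes is a legitimate question and needs no third arm. The lack of one limits only what can be said about each programme on its own.

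**Conclusion.** The concern holds as an inconsistency between the conclusion announced in the Discussion and the aim and power calculation. The sample size is right for the stated aim. A non-significant result at 64 per arm would not show equal effectiveness: it is expected about 80% of the time at a true 0.2 SD deficit and about 61% at 0.3 SD, with a 95% CI half-width of about 0.35 SD. Only a margin near 0.5 SD has about 80% power.

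These figures assume full data, a simple two-arm comparison of means and, for the non-inferiority power, a true difference of zero. All margins and SDs are assumptions.

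One caveat goes with this. Similar change in two active arms would fit two programmes that work or two that do not, so conclusions, including the hoped-for reduction in decline, can only be relative ones between the arms. Severity is moderate: the correction concerns what may be concluded.

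**What to change.** 1. Reword the Discussion sentence to match the Background aim and the Abstract: the trial tests whether including the person with dementia gives better cognitive outcomes than training the companion alone.
2. Add that a non-significant result will not be read as equal effectiveness, and that the between-arm difference will be reported with its 95% confidence interval.
3. If the equal-effectiveness claim is kept, justify and fix a non-inferiority margin before unblinding, make the claim only if the 95% confidence interval excludes that margin, and state the power at the planned size under a stated SD.
4. Limit statements about reduced decline to differences between the arms.

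Items 1, 2 and 4 change only wording, and the sponsor gives up or qualifies one conclusion. Item 3 can cost more. Keeping 128 dyads means accepting low power unless the margin is near 0.5 SD, while 80% power would need 350 dyads for a 0.3 SD margin and 786 for 0.2 SD.
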